### Outcome measures

The outcome measures for the pilot trial include the following:
Recruitment measures: We will calculate the number of participants who respond to the research call and are screened for eligibility, number/proportion of screened participants who meet the criteria for eligibility, number/proportion of eligible participants who provide consent and are enrolled in the study, average time taken to enroll the required number of study participants, and reasons for any delays, reasons for non-consent, and primary reasons for non-eligibility.Study implementation and fidelity measures are as follows:*Individual and education:* Number of church members who request copies of the study materials. Proportion of enrolled church members who receive the cookbooks/exercise manuals/CDs, admit to using them, how often they are used, the self-rated usefulness of the materials in relation to study outcomes, and reasons for non-use.*Church committees and group events*: Number of nominated committee members who consent to participate in the church project committees, number of consenting members who remain as members throughout the study period, attendance at church events, and rated usefulness of project events in relation to trial outcomes.*Peer Counselors*: Number of church members who volunteer to serve as peer counselors, proportion of potential peer counselors who attend the training, proportion of trained MI counselors who satisfy the post-training evaluation, and proportion of trained peer counselors who remain in the program.*Church policy:* We will assess the perception of the selected church policies and perceived level of policy compliance.*Faith based text messages*: We will calculate the proportion of study participants who received, opened, and read the messages; participants’ ratings of messages in relation to trial outcomes.*Overall study fidelity of intervention delivery*: This will be assessed based on the delivery of each of the intervention components as stated in the study protocol and action plan. We will measure this using a structured checklist by direct observation of the implementation of each of the intervention components, noting any deviations from protocol/action plan.3.Retention measures: This will be calculated as the proportion of committee members, peer counselors, and enrolled study participants who remain in the study at 3 and 6 months. We will also assess reasons for attrition among the study drop-outs.4.Data collection measures: We will assess the proportion of completed surveys, time taken, and number of visits/phone calls/reminders required to complete surveys, levels of missing data, and reasons for incomplete surveys and variable missingness.5.Data required for sample size estimations for a future definitive trial: These will be measured by computing the intracluster correlation coefficient (ICC), effect size estimates, variances, and 95% confidence intervals for the potential differences between the study arms at baseline and follow-up.6.Acceptability and program satisfaction measures: We will measure program satisfaction using a self-reported rating among study participants. This will be done for each of the components of and the overall adapted intervention.7.Measures for the end-points and psychological mediators for the proposed definitive trial: We will also collect data on the primary and secondary end-points for the proposed definitive trial and assess the process of collecting this data. In the parent trials, the primary outcomes were the number of servings of fruit and vegetables (F&V) and the minutes of moderate to vigorous PA per day (MVPA). The secondary outcomes included food consumption, vegetable preparation practices, intrinsic/extrinsic motivation, and self-efficacy to eat F&V and to increase MVPA. The main trials also assessed psychological mediators like physical well-being, depression, and religiosity indices. As with the parent trials, we will use a modified version of the National Cancer Institute (NCI) F&V food frequency questionnaire to assess food intake over the past month [51–53]. Vegetable preparation practices, self-efficacy, and other health habits will be assessed with an adapted version of the instruments developed for the eat for life program [54]. Intrinsic/extrinsic motivation will be assessed with an adapted version of the treatment self-regulation questionnaire (TSRQ) measure [55]. Physical activity and sedentary behavior will be assessed using adapted versions of the International Physical Activity Questionnaire (IPAQ) and WHO STEPS tools [56, 57]. Psychological mediators like physical well-being will be measured using the widely used single item measure on self-health [58]. Depression will be assessed using the patient health questionnaire-9, previously validated for use in this setting [59, 60], while religiosity and organized religious activity will be measured with two variables, church attendance, and private prayer frequency [61].

### Sample size estimation

In a pilot trial, the objective is not necessarily to prove superiority of the treatment but to test trial procedures and processes and to obtain estimates of parameters for the main trial sample size calculation. Therefore, standard sample size formulae which are used for main treatment assessments are not usually applicable to pilot trials [62, 63] see Additional file 1. As recommended in the CONSORT guidelines for publishing protocols of pilot studies [62], we made a pragmatic decision to select 12 churches for the study and 25 participants per church based on our knowledge of the church structure, its demographics, and our pilot objectives.

### Recruitment and retention strategies

Churches will make announcements for participation in the project, during church services, and using bulletin inserts or other usual means of communication. Trained church volunteers and/or research assistants will help to recruit interested participants. This will be based on participant eligibility and on a first-come, first-served basis. Recruited participants from each church will be selected to participate in the individual program activities and complete the surveys. Participant recruitment will be conducted in the three study arms in the same manner regardless of treatment allocation.

To promote participant retention, we will provide a small incentive (a gift worth $5 or less) to all participants regardless of the treatment arm. In addition, participants will receive at least two text messages and one phone call reminder to schedule a date for the follow-up surveys. We expect to be able to complete participant enrolment over a period of 12 weeks and will aim for at least 80% retention at the 6-month follow-up, noting any differences in attrition rates between study groups.

### Data collection

Study data will be collected at three-time points (at baseline, then 3 and 6 months after) (Table 2). The adapted questionnaires will be completed in the church premises either before or after a routine church program, or as is convenient for the participant. Participants will have the choice of filling in questionnaires by self-report or with the assistance of a trained interviewer and in their preferred language. Survey tools will be translated and back-translated into the preferred language of the parishioner if the need arises. Participants not responding to the follow-up questionnaires will be contacted on the telephone by the trained interviewers and offered to complete the instrument either by a scheduled home visit or over the phone. We will analyse participants’ responses for those completing the instruments by self-report, with the help of trained interviewers and by phone to observe for any statistically significant differences. At the end of each data collection session, we will ask the participants to rate their level of satisfaction with the data collection process. We will also note the time taken and number of visits required to complete each data collection session. At the end of the study, participants will fill a brief survey to assess their self-reported exposure, overall program satisfaction, and individual satisfaction with each of the program components. Figure 2 shows the study flow chart for participant enrolment, baseline data collection, follow-up, and analysis & Table 2 shows schedule of enrolment, interventions and assesements

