### Data analysis:

#### Quantitative data analyses

As this is a pilot study, significance tests of change over time will not be performed on the primary or secondary outcomes. The main analysis will focus on descriptive statistics relating to feasibility to estimate likely recruitment, retention, and participation rates. These will be represented by point estimates and 95% confidence intervals. We will compute the intra class correlation coefficient, effect size, and variance and use these in addition to estimates derived from the literature to estimate a sample size required for a definitive trial, if deemed appropriate. Quantitative data will be analyzed using STATA 15.0

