#### Success indicators

The rationale for the success indicators was based on the process values obtained in one of the parent trials, where the process trial yielded 65.8% member participation and 100% church participation rates [64]. The success indicators for this pilot feasibility trial would be to:
Successfully develop a culturally adapted version of the two RTI as evidenced by a clearly defined BSS and BSS^+^ action plan approved by the church leadership and committee members.Achieve the 70% recruitment targets for churches, church volunteers, and study participants and the time used to meet these targets.Successfully deliver the adapted intervention to at least 70% of the selected churches.Church compliance with at least 70% of the intervention components and respondent participation in at least 70% of the components.Church retention rate of 100% at 6-month follow-up and at 70% or more for church committee members, volunteers, and study participants at 3 and 6 months.Data completion rates and data completeness of ≥ 70% for each outcome measure and data collection method.

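### Differences between data-collection modes are to be judged by statistical significance, although participants choose the mode and phone goes only to follow-up non-responders, so neither a significant nor a null result isolates a mode effect

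*Protocol article*

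**What the plan says.** The Data collection section of the protocol article describes three ways of completing the questionnaires and how people come to use each.

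- **Self-completed or interviewer-assisted:** "Participants will have the choice of filling in questionnaires by self-report or with the assistance of a trained interviewer".
- **Phone:** this route starts from non-response at follow-up: "Participants not responding to the follow-up questionnaires will be contacted on the telephone by the trained interviewers". As described, phone completers are a self-selected part of the follow-up non-responders, since a home visit is the alternative.
- **Analysis:** responses completed by the participant alone are to be compared with those completed "with the help of trained interviewers and by phone to observe for any statistically significant differences". Significance is the only criterion stated for this comparison.

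The fourth item under Study objectives asks how accurate the data collection methods are, what influences that accuracy, and what follows for a fully powered trial. The endpoints proposed for that trial, fruit and vegetable servings and minutes of moderate to vigorous activity, are collected by questionnaire (Outcome measures).

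**The concern.** Mode is not assigned in this pilot. The first two modes follow preference, which may go with literacy, language or age. Phone follows non-response and, as described, arises only at follow-up. A significance test across modes therefore compares different kinds of people as well as different modes, and its result does not say which of the two produced the difference. A larger sample would not cure this; it would make a pure selection difference more likely to reach significance.

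The opposite result is no more informative. The sample was set pragmatically, and the phone group may be small. A non-significant result would then be compatible with a sizeable mode difference.

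At stake is whether this comparison can inform the accuracy objective. Mode may also be used unevenly across arms, for instance if non-response differs by arm. A mode effect could then enter the arm differences, variances and intracluster correlation that the pilot is meant to supply for planning.

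**Working it through.** The article states no power, effect size or mode split for this comparison, so there is no figure to reproduce. The calculations below show what a significance criterion could and could not reveal.

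**Inputs from the article**
- Sample size (Sample size estimation): "we made a pragmatic decision to select 12 churches for the study and 25 participants per church", so 12 × 25 = 300 participants.
- Retention aim (Recruitment and retention strategies): the study "will aim for at least 80% retention at the 6-month follow-up", so 0.80 × 300 = 240.
- Retention threshold (Success indicators): "at 70% or more for church committee members, volunteers, and study participants at 3 and 6 months", so 0.70 × 300 = 210.

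**Assumptions not in the article**
- Phone share of 10%, 20% or 30% of follow-up respondents.
- Two-sided 5% test, 80% power, normal approximation, differences in SD units, clustering ignored.

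**1. What a null result can exclude (phone versus all others)**

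Detectable difference = (1.96 + 0.84) × √(1/n₁ + 1/n₂) = 2.80 × √(1/n₁ + 1/n₂).

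| Follow-up n | Phone share | n₁ vs n₂ | √(1/n₁ + 1/n₂) | Detectable difference |
|---|---|---|---|---|
| 240 | 10% | 24 vs 216 | 0.215 | 0.60 SD |
| 240 | 20% | 48 vs 192 | 0.161 | 0.45 SD |
| 240 | 30% | 72 vs 168 | 0.141 | 0.39 SD |
| 210 | 10% | 21 vs 189 | 0.230 | 0.64 SD |
| 210 | 20% | 42 vs 168 | 0.173 | 0.48 SD |
| 210 | 30% | 63 vs 147 | 0.151 | 0.42 SD |

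These figures pool self-completed and interviewer-assisted forms as the comparator. Phone versus self-completed alone has a smaller comparator. With 240 followed up, 5% to 20% by phone and the rest split 50:50 or 80:20 between self-completion and interviewer, power at a true difference of 0.3 SD is 17% to 44%.

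**2. Self-completed versus interviewer-assisted at baseline (n = 300)**

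By the same formula the detectable difference is 0.32 SD for a 50:50 split (150 vs 150) and 0.54 SD for 90:10 (270 vs 30). Power at 0.5 SD runs from 99% down to 74%. Low power is therefore not general: it depends on the contrast and the split.

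**3. What a significant result can mean**

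Suppose mode has no effect on answers, but the people in two mode groups differ by 0.3 SD through self-selection (an illustrative value). The chance of significance is about Φ(0.3/SE − 1.96), with SE = √(1/n₁ + 1/n₂):

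- 24 vs 216: Φ(0.3/0.215 − 1.96) = 29%
- 48 vs 192: Φ(0.3/0.161 − 1.96) = 46%
- 120 vs 120: Φ(0.3/0.129 − 1.96) = 64%

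The total is 240 in each line. The better balanced, and so the more powerful, the comparison, the more often selection alone is declared significant.

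**The case against.** The strongest reply is that this is one exploratory sentence in a pilot that does not claim to be powered for any comparison. The article names no test and does not say that the comparison is unadjusted; covariates and clustering may properly sit in a fuller plan. The accuracy objective also draws on other evidence: completion rates, missingness, time and visits needed, satisfaction ratings, and focus groups with participants and data collectors. This stands, and it keeps the point modest. It does not rescue the stated criterion, because significance is a poor basis for judging mode whether or not a model lies behind it.

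Stronger readings are tempting, but the documents do not support them.

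- **That the mode test contradicts the analysis section.** Quantitative data analyses says only that "significance tests of change over time will not be performed on the primary or secondary outcomes". Comparing collection modes is a different question, so there is no conflict.
- **That a null result will be used to pool modes in the definitive trial.** No section attaches any decision to this comparison. Progression rests on the success indicators and the qualitative findings, and neither includes a mode test.
- **That a mode bias larger than the intervention effect could be missed.** The article gives no expected effect or SD, so the two cannot be compared.
- **That the comparison is underpowered without qualification.** This rests on assumed phone shares, and it fails for a 0.5 SD difference between self-completed and interviewer-assisted forms unless the split is very uneven.

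**Conclusion.** The point holds as a limited one: the criterion stated in Data collection cannot answer the question it serves. Confounding of mode with the person follows directly from the way modes are chosen or offered, and needs no numerical assumption.

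The size of what a null result could miss is conditional. With 240 followed up and 10% to 30% by phone, only phone-versus-others differences of about 0.6 to 0.4 SD are detectable with 80% power; with 210 the range is 0.64 to 0.42 SD. Clustering is ignored, and it would matter to the extent that a mode is concentrated in particular churches. This is a secondary process question in a pilot, and changing it is a cheap improvement rather than the repair of a main analysis.

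**What to change.** In Data collection, replace the search for significant differences with the following.

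1. Record the mode of completion on every form, and tabulate mode by arm and time point.
2. Report follow-up mode differences as estimates with 95% confidence intervals, adjusted for the participant's baseline value and the characteristics collected, with church as a random effect or with cluster-robust standard errors.
3. Label the estimates observational, meaning that they do not separate mode from selection.
4. State that a non-significant difference will not be taken as evidence that modes are equivalent.

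There is no need to hold each participant to one mode across all three time points. That would not fit the phone route, which exists as a fallback after non-response.

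The cost is a mode field on each form and minor analysis work, with no new participants or visits. The limitation is that adjustment reduces selection but does not remove it, particularly the selection that comes from non-response itself.

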**Table 2 Tab2:**
[figure not shown]
Schedule of enrolment, interventions, and assessments

*t*_1_ baseline, *t*_2_ 3 months, *t*_3_ 6 months

We will also conduct a series of focus group sessions to qualitatively assess the implementation measures. We will hold sessions with the study participants to obtain their feedback about their opinions and experiences of the BSS and BSS+ programs and processes, including the facilitators and barriers to participant retention. We will collect information on participants’ experiences of the intervention and its components challenges with completing questionnaires, their concerns about the quality and delivery of each of the intervention components, and any potential impediments to the successful initiation of a definitive trial. We will conduct additional focus group discussions with the data collectors, peer counselors, and the members of the steering committees to obtain their feedback of the study processes, experiences with the program, and the challenges they may have experienced with adhering to the protocol.

### Data analysis:

#### Quantitative data analyses

As this is a pilot study, significance tests of change over time will not be performed on the primary or secondary outcomes. The main analysis will focus on descriptive statistics relating to feasibility to estimate likely recruitment, retention, and participation rates. These will be represented by point estimates and 95% confidence intervals. We will compute the intra class correlation coefficient, effect size, and variance and use these in addition to estimates derived from the literature to estimate a sample size required for a definitive trial, if deemed appropriate. Quantitative data will be analyzed using STATA 15.0

#### Success indicators

The rationale for the success indicators was based on the process values obtained in one of the parent trials, where the process trial yielded 65.8% member participation and 100% church participation rates [64]. The success indicators for this pilot feasibility trial would be to:
Successfully develop a culturally adapted version of the two RTI as evidenced by a clearly defined BSS and BSS^+^ action plan approved by the church leadership and committee members.Achieve the 70% recruitment targets for churches, church volunteers, and study participants and the time used to meet these targets.Successfully deliver the adapted intervention to at least 70% of the selected churches.Church compliance with at least 70% of the intervention components and respondent participation in at least 70% of the components.Church retention rate of 100% at 6-month follow-up and at 70% or more for church committee members, volunteers, and study participants at 3 and 6 months.Data completion rates and data completeness of ≥ 70% for each outcome measure and data collection method.

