### Description of the intervention arms

A.Body, Soul, and Spirit will be modeled after the two EBIs conducted in African American churches in the USA: the “Body and Soul” and the “Healthy Body Healthy Spirit” [32, 33]. The adapted intervention, Body, Soul, and Spirit, will involve a combination of the core components of both of the parent interventions. In creating the aggregate intervention, we will select components of each of the parent trials that were deemed “essential” [38, 39]. A component was termed “essential” if it was reported to have accounted for the positive intervention effects observed in the parent trials [40, 41]. The following components of the parent trials were considered essential and will be considered for our adaptation and use (see Table 1):

a) Individual education
i.An adapted version of a cookbook [32] with healthy eating recipes, cooking techniques, storage tips for fruits and vegetables, and health benefits of increasing fruit and vegetable intake.ii.An adapted version of an exercise manual [33] and exercise video or audio CD [33] containing gospel music with biblical quotes/themes and/or brief sound bites of priest sermons sliced between songs.

b) Group education

Each participating church will receive a single copy of an adapted version of “Forgotten Miracles” [32] an 18-min video that targets fruit and vegetable intake using both spiritual and secular motivational messages. Churches will be asked to organize public screenings of the video and to make the copy available to members on request.

c) Campaigns and promotions
i.Formation of a project coordination committee: This committee will be composed of representatives of the academic and church communities and will be responsible for the implementation of the project [32, 33].ii.Church events: There will be a project kick-off event, at least one nutrition event and an additional event involving the church priest [32]. Examples of events included in the parent trials are serving fruit and vegetables after church services, at other church programs, or during the kick-off event; sponsoring food demonstrations or taste tests; organizing tours of food markets and inviting guest speakers; or having priest sermons related to health (Table 1).

**Table 1 Tab1:** Intervention components of the parent trials and adapted interventions

	Parent Trial		Adapted Intervention		

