B. Body Soul and Spirit Plus (Bss+) will retain all the components of BSS with the addition of faith-based text messages. We will develop the content, wording, frequency, and timing of each message guided by the theoretical models mentioned above, a review of existing literature and the feedback received from the parishioners. We will then pre-test them among a small group of parishioners before use to ensure that the messages are designed to have the desired effect. The project coordinator and/or trained church volunteers will send these messages periodically at pre-scheduled intervals.

C. Usual care/Control: Information leaflets on healthy food consumption and physical activity will be distributed to parishioners in the churches in this group after a church service. This will constitute an information-based *standard of care* approach that will be used as the control condition for this group randomized trial (See Fig. 2).

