#### Phase 1—pre-implementation

*i*) *Community entry, church recruitment and randomization:* We will work with the leadership of the diocese to recruit the 12 eligible churches from their network of churches. To be included in the study, churches must have at least 100 active members (we define “active” as members who attend church services at least weekly). We will obtain a list of the churches in the diocese and screen them for eligibility. Then, we will randomly select 12 eligible churches from this list. Selected churches will be allocated into one of three groups: BSS, BSS+, or control. Randomization will be computer-generated, with allocation concealment by opaque sequentially numbered sealed envelopes. An independent biostatistician will generate the randomization sequence in accordance with the CONSORT guidelines [42].

*ii*) *Partnership development and Capacity building:* We will create a diocesan-project steering committee (DPSC) consisting of one representative from the diocesan leadership, one representative of the diocesan medical society, two diocesan volunteers, and members of the academic research team. The DPSC will serve as the overall planning and coordination team for the intervention. In addition, in each of the eight intervention churches, we will create a local church implementing committee (LCIC), which will consist of at least two church members who are either volunteers and/or persons nominated by the vicar and members of the academic research team. The LCIC will serve as the in-house implementation team for the intervention.

Once the committees have been constituted, we will conduct a partnership development and capacity building workshop for committee members to obtain leadership and community buy-in. Workshops will initially focus on sharing the project aims with participants to obtain their support and commitment and to engage them as partners on the project. The committees will hold regular meetings where the academic researchers will work with them to identify effective ways of implementing the intervention. Thereafter, the committee members will meet at regular intervals to discuss the development, planning, and implementation of the project. Committees will decide on operational procedures and develop a plan to keep their church parishioners involved in the intervention.

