#### Phase 3: intervention delivery/implementation

We will employ a three-arm group randomized pilot study design using 12 churches (4 in each group). The intervention will operate at two levels. The church-wide events and environmental changes will be aimed at the entire congregation, while the distribution of exercise/nutrition videos, manuals and cookbook recipes, audio CDs, and text messages will be delivered only to individuals who voluntarily enroll and consent to participate in the study. Data will be collected at baseline 3 and 6-month time points.

Each participating church will identify 2–3 volunteers to serve as peer counselors for this project. They will participate in the recruitment of study participants and undergo peer-counselling training for the program. Volunteers will have a background in a “health-related profession” (e.g., physician, nurse, or other health worker) and will be required to attend a training, make four intervention calls to at least five members of each church, and undergo a performance evaluation before engagement. This training will provide knowledge and general skills in patient recruitment, research ethics, and motivational interviewing techniques like asking open-ended questions, reflective listening, and specific strategies to elicit discussions about PA and HFC. They will be asked to recruit and make at least four intervention calls to at least five study participants. Peer counselors will receive a small stipend for their time and effort with participant recruitment and retention and calling cards to cover the cost of the phone calls. In addition, regardless of the treatment arm, churches (rather than participants) that achieve the minimum targets for participant recruitment and retention will be provided with an incentive worth $100 or less at the end of the study.

#### Phase 4

Implementation evaluation—This will involve quantitative and qualitative data collection and analysis of implementation measures (i.e., participant recruitment and retention; Program participation and satisfaction and data collection completion), the calculation of parameter estimates for subsequent sample size calculations for the future trial, evaluation of the program success criteria, and a decision to determine whether or not to progress to a definitive trial.

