#### Qualitative data analyses

Audio-recorded interviews and focus groups will be transcribed verbatim, and we will perform a content analysis using standard thematic analytic techniques. At least two independent researchers will code each transcript before subsequent summarization and interpretation. Data will be analyzed with the Dedoose 8.18. software [65].

Collectively, these will provide information on the feasibility of the intervention implementation, trial procedures, data collection methods, and the overall acceptability of the intervention. The achievement of the success criteria stated above, in addition to the qualitative information generated from this pilot, will be considered in deciding whether or not to proceed with the intervention, with or without amendments. We will note which amendments to consider in developing a refined version of the intervention protocol for a fully powered trial to measure the effect of BSS and BSS+ on physical activity and fruit and vegetable consumption among church members.

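### As worded, the 70% delivery indicator cannot be met: only 8 of the 12 selected churches (66.7%) are assigned the adapted intervention

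*Protocol article*

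**What the plan says.** The third item in the list under Success indicators is to "Successfully deliver the adapted intervention to at least 70% of the selected churches".

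Phase 1, on church recruitment and randomisation, shows which churches the term covers. After screening the diocesan list, the plan is: "Then, we will randomly select 12 eligible churches from this list". The next sentence reads: "Selected churches will be allocated into one of three groups: BSS, BSS+, or control". The Abstract likewise describes the 12 churches as randomly selected, with four per arm.

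The allocation is stated again under Phase 3: "We will employ a three-arm group randomized pilot study design using 12 churches (4 in each group"). When Phase 1 turns to the churches that will run the programme, it uses a different expression: "in each of the eight intervention churches, we will create a local church implementing committee (LCIC").

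The section describing the intervention arms says what is to be delivered: "The adapted intervention, Body, Soul, and Spirit, will involve a combination of the core components of both of the parent interventions". BSS+ is that package with faith-based text messages added. The control arm gets leaflets, of which the same section says: "This will constitute an information-based *standard of care* approach that will be used as the control condition for this group randomized trial".

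The last paragraph of Qualitative data analyses gives the indicators their role. Meeting them, together with the qualitative information, "will be considered in deciding whether or not to proceed with the intervention, with or without amendments".

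**The concern.** The numerator and denominator of this indicator come from different sets of churches. The numerator can include only churches assigned BSS or BSS+. The denominator, in the article's own usage, also includes the control churches. With one third of the churches in the control arm, the proportion is capped at two thirds, which is below the 70% required.

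Assessing whether the adapted programmes can be implemented is the stated aim of the pilot, and this is the indicator that addresses delivery at church level. A threshold that returns a miss even under flawless delivery tells the team nothing when it decides whether to move to a definitive trial. Someone applying the list literally would also report a failure that did not occur.

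**Working it through.** **Inputs**

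- Churches selected and randomised: 12 (Phase 1; Trial design; Phase 3).
- Arms: 3, with 4 churches each (Trial design; Phase 3).
- Churches assigned the adapted intervention: 8 (Phase 1, partnership development).
- Threshold: at least 70% (Success indicators).

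**Step 1: reproduce the article's counts.** 3 arms × 4 = 12 churches, and 2 intervention arms × 4 = 8. Both match the text.

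**Step 2: highest attainable value as worded.** Maximum = churches assigned the intervention / churches selected = 8/12 = 0.667, or 66.7%. This is below 70%.

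**Step 3: churches needed as worded.** 0.70 × 12 = 8.4, which rounds up to 9 of 12 (75%). Only 8 churches are assigned the intervention, so the shortfall under perfect delivery is 9 − 8 = 1 church.

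**Step 4: the same threshold on the eight intervention churches.** 0.70 × 8 = 5.6, which rounds up to 6 of 8 (75%). Five of eight is 62.5% and falls short.

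**Step 5: how the two denominators classify the same delivery.**

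| Churches with delivery | Out of 12 | Out of 8 |
|---|---|---|
| 5 | 41.7%, not met | 62.5%, not met |
| 6 | 50.0%, not met | 75.0%, met |
| 7 | 58.3%, not met | 87.5%, met |
| 8 | 66.7%, not met | 100%, met |

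The two readings disagree for every result from 6 to 8 churches. On a denominator of 12, no result meets the indicator.

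**Step 6: could leaflets count as delivery?** Table 1 appears to place the control column under its heading for the adapted intervention, and leaflets go to all three arms. If leaflets counted, 12/12 would be possible. The arm descriptions rule this out: they identify the adapted intervention with Body, Soul, and Spirit and treat the leaflets as the control condition.

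**The case against.** The strongest reply is that the indicator can sensibly mean only the eight churches. An intervention can be delivered only where it is assigned, Phase 1 itself counts eight intervention churches, and the next indicator, on compliance with intervention components, also makes sense mainly for those churches. The article uses the word selected loosely elsewhere, for parishioners, policies and participants, so it is not a formally defined term. Much of this stands: the eight churches are very probably what was meant. But that reading has to be inferred. No sentence limits the denominator, and where the word is applied to churches it covers all 12.

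A reader might go further than the text allows in three ways.

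- *That the pilot is bound to fail its progression decision.* The article does not support this. The criteria are to be considered together with qualitative information, proceeding with amendments is an option, and nothing says that missing one of six indicators stops progression.
- *That the authors could choose the denominator to suit the results.* This is weak. A denominator of 12 is unattainable whatever the data show, so the only usable choice follows from the design and not from the results.
- *That needing 6 of 8 (75%) is itself an error.* It is not. Any percentage applied to eight churches rounds up to a whole church.

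**Conclusion.** The point holds as a wrong threshold in one sentence. As worded, the indicator requires 9 of 12 churches when only 8 can receive the adapted intervention, so the best possible result is 66.7% against 70%. This rests on two readings, both taken from the article: that selected churches means the 12 that are randomised, and that the adapted intervention means BSS or BSS+. It needs no outside figure.

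Severity is moderate to low. The likely intention is clear, the indicator is one of six, and it is not a binding stop rule. Randomisation, sample size, data collection and the parameter estimates for the definitive trial are unaffected. It is still worth correcting, because the article states a specific threshold that conflicts with its own allocation; this is not a detail left to an analysis plan.

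**What to change.** Reword the third success indicator along these lines: *deliver the adapted intervention in at least 70% of the eight churches randomised to BSS or BSS+ (that is, at least 6 of 8)*.

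Naming the denominator cures the fault, and giving the count removes any doubt about rounding. No minimum per arm is needed. The protocol contains no such requirement, and adding one would change the decision rule: full delivery in one arm (4 of 4) and delivery in 2 of 4 churches in the other gives 6/8 = 75%, which meets the stated 70%.

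The cost is one sentence, with no change to the design or conduct of the pilot.
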